### Training Paradigms

#### Hands-Free Body Weight Support Gait Training

This group served as our “control,” in that participants did not perform any additional essential challenging mobility skills during their 6-week training period. We felt that the inclusion of an active training control group was necessary to determine if adding essential challenging mobility skills practice to a gait training program would improve walking outcomes above and beyond improvements gained from walking practice alone. However, it is important to note that because of the safety features of our robotic device, we were able to eliminate provision of handrail support and/or manual assistance from the clinician. Although walking upright with handrail support can provide sufficient training challenge and fall safety, because of poor hemiparetic trunk control stroke, survivors are likely to adopt stooped postures by leaning forward and holding onto handrails for trunk support [40]. Such postures not only decrease training intensity and metabolic output but also minimize functional improvements [41,42]. Thus, treadmill training without handrail support can offer a more practical dynamic balance challenge that pertains to real-world independent ambulation. In addition, we did not offer participants any walking instructions (eg, how to step or correct their movements) and did not offer any passive assistance during training. Our governing principle regarding walking rehabilitation post stroke was to provide the individual with a safe environment to practice walking, solve the problem, and learn from mistakes during training. We followed AHA guidelines for exercise training [16]. Participants in this group walked for a total duration of 30 min per session, at 60% to 80% of their heart rate (HR) reserve (ie, moderate to high intensity) based on the Karvonen formula [43] with or without their prescribed BWS level (ie, between 0 and 30% support; assigned as described below). By taking advantage of the KA interface’s safety mechanism and DOF, participants in this group were able to explore their limits of stability while controlling the treadmill belt speed, and thus, train independently without assistance or external support.

#### Challenge With Hands-Free Body Weight Support Gait Training

This group served as our “experimental” group, in that participants additionally performed 9 different essential challenging (C) mobility skills, along with HF walking during their 6-week training period (Table 1). The purpose of practicing these 9 essential training challenges along with HF walking was to offer participants opportunities to navigate through common environmental hazards that they may encounter during community ambulation. This protocol was innovative, as it involved exposing stroke survivors to challenging tasks that required strong skills in anticipatory and reactive balance and functional mobility. The KA’s safety features allowed us to provide participants with this experience and to treat losses of balance or stumbles as “learning experiences,” from which participants could learn to formulate new strategies without any negative consequences. At the start of each training week, the program coordinator would randomly select and assign 3 challenges for each session using a random number generator [27]. Participants practiced training for each of the 3 skills for 30 min (10 min per skill), without handrail support at 60% to 80% of their HR reserve intensity per session. We did not have a prescribed challenge progression for each skill; however, we encouraged participants to perform each skill at a level that was challenging for them (see task difficulty, Table 1).

### Intervention Protocol for Each Training Session

This training protocol comprised 6 weeks of 18 total training sessions for both groups (summary in Table 2). Each group trained 3 times per week with alternate rest days to prevent undue fatigue.

### Participant Body Weight Support Level Determination for Each Training Session

We used a unique approach to determine BWS levels for all participants for each training session. Instead of automatically applying a specific level of BWS for all participants, we instead allowed BWS to vary per training day, depending on the participant’s fastest CWS inside the device. At the start of each session, participants walked in the self-drive mode for 5 m at 4 different levels of BWS (0%, 10%, 20%, and 30%). Some of the taller individuals were unable to use 30% because of height constraints of the KA (n=5). We calculated 10-m walk speed at each level of BWS and selected the participant’s fastest CWS using a speed difference of ≥0.08 m/s faster than 0%. The participant used this level of BWS to train for the session. This method ensured each participant’s BWS levels were individualized, unbiased, and varied according to their optimal walking speed performance. We were interested in whether participants would gradually decrease BWS over the duration of the training protocol.

### Participant Training Intensity Heart Rate Zone Determination for Each Training Session

We documented all participant’s baseline blood pressure and HR before commencement of each training session. We calculated the maximum HR for each participant using their age (ie, HR_max_=220 − age) and calculated the desired 60% to 80% training intensity using the Karvonen formula (ie, training intensity=(max HR − resting HR) × (desired %) + resting HR) based on AHA training recommendations [16]. If the participant was taking a beta-blocker, we revised this formula to use a max HR calculated as HR_max_=164 − age [44]. Thus, we individually customized the participant’s training intensity for each session. We encouraged participants to walk fast enough during training to achieve these zones; however, we also measured rating of perceived exertion (RPE; see below) to obtain a proxy measure of training intensity in the event that HRs did not reach the desired intensity. We used a GARMIN HR monitor that was strapped to each participant’s chest to record actual HR measurements for each session. We recorded HR values each minute; thus, we recorded a total of 30 HR values per training session (6 × 5-min bouts=30 min).

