### Initial Screening

An experienced physical therapist, blinded to the training interventions, evaluated all consented participants using our study inclusion or exclusion criteria to approve participants for study enrollment (Textboxes 1 and 2).

Study inclusion criteria.Age 19 years and above, community-dwelling, unilateral stroke survivorsHistory of cerebrovascular accident (ie, ischemic or hemorrhagic) confirmed by computed tomography, magnetic resonance imaging, or clinical criteriaAt least 5 months after stroke incidentAble to ambulate at least 14 m with/without an assistive device or the assistance of one person, with a self-selected comfortable walking speed of ≤1.0 m/sAble to demonstrate receptive and expressive communication ability.Primary care physician approval for exercise (obtained via the Health Insurance Portability and Accountability Act, that is, HIPPA-approved guidelines)Willing to provide voluntary informed consent

Study exclusion criteria.Presence of serious or uncontrolled cardiovascular conditionsResting systolic blood pressure >180 mm HgResting diastolic blood pressure >110 mm HgResting heart rate >100 bpmHistory of uncontrolled arrhythmias/angina/syncopePresence of amputations and/or any severe musculoskeletal problems that restrict walking, for example:Recent fractures of the lower limbOpen wounds/abscessUse of spasticity management drug therapies for affected lower limb before participation, for example:Botulinum toxin injection (<4 months earlier)Phenol block injection (<12 months earlier)Intrathecal baclofen or oral baclofen (within the past 30 days)Any cognition involvement impairing ability to follow instructions and/or Mini-Mental State Exam Score <24Past participation in any study examining the effects of long-term body weight support treadmill training in (>4 weeks of training); limb-loaded pedaling or lower extremity strengthening; or enrolled in any ongoing study that evaluates lower extremity functionParticipant was unable to arrange for transportation to the study site for all evaluations and intervention sessionsParticipant planned to move out of the area within 18 from the time of study enrollment

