Session design	5-min bouts × sets, or as long as continuously tolerated	5-min bouts × 6 sets, or 10-min bouts × 3 sets to allow for skill changes
Session goal	Target 60% to 80% of heart rate reserve during all trials	Target 60% to 80% of heart rate reserve during all trials
Locomotor challenge	Hands-free and without manual assistance	3 new randomized locomotor total challenges per day × 3 sessions=9 per week
Instruction	Maintain heart rate in the target zone while walking	Maintain heart rate in the target zone while performing different walking skills
Physiological measures monitored	Heart rate—using heart rate, monitor each minute; rate of perceived exertion—using Borg scale every 2 min; blood pressure—pre/post	Heart rate—using heart rate monitor each minute; rate of perceived exertion—using Borg scale every 2 min; blood pressure—pre/post
Additional session measurements	Total number of steps (using step watch) and distance covered (using distance wheel)	Total number of steps (using step watch) and distance covered (using distance wheel)
Rest breaks	Every 5 min if necessary; standing breaks if heart rate exceeded zone; voluntary breaks if requested by participant (rare)	Every 5 min if necessary; standing breaks if heart rate exceeded zone; voluntary breaks if requested by participant (rare)
Training personnel	Physical therapist × 1; research assistant × 1	Physical therapist × 1; research assistant × 1
Training setting	Clinical laboratory	Clinical laboratory

^a^BWS: body weight support.

^b^10MWT: 10-meter walk test.

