### Subgroup Analysis

In addition to these main assessment measures, we also recorded BWS levels, HR, and RPE exertion changes, total number of steps, and distance covered during each session, for participants in both training groups. Descriptive data analysis along with subgroups comparative analysis will be performed on these variables, from pre- to postintervention and on a week-by-week basis, and will be reported in another manuscript. We will also assess feasibility and compliance of each group to either intervention, along with ability to maintain target HR intensity during training. These subgroup analyses will help in better understanding the impact of training on functional walking outcomes and impact on community ambulatory function.

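### For some eligible beta-blocker users the printed maximum of 164 − age gives a very narrow, zero or negative heart rate reserve, so the target zone, the break rule and the target-HR result do not fit together

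*Protocol article*

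**What the plan says.** The Methods section on determining the heart rate zone gives two age-based maxima. The general one is "We calculated the maximum HR for each participant using their age (ie, HR_max_=220 − age"). The other is for beta-blocker users: "If the participant was taking a beta-blocker, we revised this formula to use a max HR calculated as HR_max_=164 − age". Either goes into the Karvonen formula, "training intensity=(max HR − resting HR) × (desired %) + resting HR". The resting value is taken at the visit: "We documented all participant’s baseline blood pressure and HR before commencement of each training session".

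Under Initial Screening, participants qualify at "Age 19 years and above" with no upper limit, and only a resting heart rate above 100 bpm excludes. Beta-blocker use is not an exclusion.

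Table 2 gives both arms the same goal, "Target 60% to 80% of heart rate reserve during all trials", and the same rest rule, "standing breaks if heart rate exceeded zone". The Subgroup Analysis section then plans to assess, with feasibility and compliance, the "ability to maintain target HR intensity during training".

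**The concern.** Taken together, the expression, the entry limit and the target admit participants for whom the calculated maximum is at or below the heart rate they have at rest. A target zone cannot be formed for them, and the article gives no rule for that case. For others on the drug the zone exists but is only a few beats wide and close to rest.

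Two later steps use the zone. The break rule is triggered when heart rate exceeds it; if the zone lies at or below rest, the resting rate already meets or exceeds it. The planned attainment result counts whether the target was held. A narrow zone near rest is easier to reach and easier to leave by overshoot than a wide one far above rest. A pooled attainment figure would then partly reflect who takes a beta-blocker.

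**Working it through.** **Inputs from the article.** Maximum: 164 − age on a beta-blocker, 220 − age otherwise. Target: rest + p × (maximum − rest), with p = 0.6 and 0.8. Eligible: age 19 or above, resting heart rate up to 100 bpm.

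**Assumed.** The particular ages and resting rates below, because the article reports no distribution of either and no count of beta-blocker users. It prints no reserve or zone in bpm, so there is no figure of its own to reproduce.

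**Boundary.** Reserve on a beta-blocker = 164 − age − rest. It is zero or below when age + rest ≥ 164:
- rest 100: age 64 or older
- rest 90: age 74 or older
- rest 80: age 84 or older
- rest 70: age 94 or older

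**Zones on a beta-blocker.** Width = 0.2 × reserve.

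| Age | Rest | Reserve | 60% value | 80% value | Width |
|---|---|---|---|---|---|
| 60 | 60 | 44 | 86.4 | 95.2 | 8.8 |
| 70 | 60 | 34 | 80.4 | 87.2 | 6.8 |
| 70 | 75 | 19 | 86.4 | 90.2 | 3.8 |
| 70 | 90 | 4 | 92.4 | 93.2 | 0.8 |
| 64 | 100 | 0 | 100.0 | 100.0 | 0 |
| 75 | 90 | −1 | 89.4 | 89.2 | −0.2 |
| 70 | 100 | −6 | 96.4 | 95.2 | −1.2 |

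In the last two rows the 80% value is below the 60% value, and both are below rest.

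**Comparison off the drug, age 70, rest 75.** Maximum 220 − 70 = 150; reserve 150 − 75 = 75. Limits 75 + 0.6 × 75 = 120 and 75 + 0.8 × 75 = 135, so 15 bpm wide, starting 45 bpm above rest. On the drug the zone is 3.8 bpm wide and starts 86.4 − 75 = 11.4 bpm above rest.

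**General shift.** At equal age and resting rate the reserve is 220 − 164 = 56 bpm smaller. The lower limit falls by 0.6 × 56 = 33.6 bpm, the upper by 0.8 × 56 = 44.8 bpm, and the width by 0.2 × 56 = 11.2 bpm.

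**If users have lower resting rates.** At age 70, a user resting at 60 has a zone 6.8 bpm wide. That is still less than half the 15 bpm of a non-user resting at 75.

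**The case against.** The case on the other side is substantial, and most of it limits the point rather than removing it.

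- **Not general.** The formula takes the resting rate measured at the session, not the entry ceiling. At resting rates of 50 to 70 bpm the reserve stays positive up to age 85, and at ages 60 to 70 with rest 60 to 70 it is 24 to 44 bpm. A non-positive reserve needs an older participant with a high resting rate, and the article does not show that this occurred. This stands.
- **Relative dose.** A reader might infer that beta-blocker users trained at a different relative intensity. The documents do not support that. The lower maximum is a deliberate adjustment for the drug, and no measured maximum is given against which to judge it.
- **Bias between arms.** A reader might also infer that the claim of similar intensity in the two arms fails. Both arms use the same expressions, target and break rule, allocation was randomized, and no imbalance in beta-blocker use is shown.
- **Primary outcome.** It is comfortable walking speed, which does not use heart rate.
- **A misprint.** The expression appears once and nothing else in the article contradicts it. Whether it was printed as intended cannot be settled from this document.
- **Perceived exertion as backup.** It was recorded in everyone, but the article names it as a proxy for heart rates that fall short of the zone. It does not address overshoot or a zone that cannot be formed.
- **Article-level detail.** Much analysis detail is deferred to later manuscripts, and that is not faulted here. The point rests on a stated rule that returns an impossible target for people the entry criteria admit.

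A percentage of minutes in zone would need a within-session standard deviation that the article does not give, so none is relied on.

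**Conclusion.** The point holds in a limited form. The printed expression, the resting-rate entry limit, the 60% to 80% target and the break rule cannot all be applied to some eligible beta-blocker users. Reserve is zero or negative when age plus resting rate is 164 or more. Below that boundary the zone can still be only a few beats wide, such as 3.8 against 15 bpm at age 70 and rest 75.

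The consequence falls on the target-HR attainment result, a feasibility measure whose meaning differs by beta-blocker use. The direction and size of the effect on the pooled figure cannot be determined, because the number of users and their ages and resting rates are not given. The bpm comparison on and off the drug assumes equal age and resting rate; the boundary needs no such assumption. This is worth correcting before the training data are reported, but it does not threaten the primary analysis.

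**What to change.** Reconcile the printed expression with the resting-rate entry limit, the 60% to 80% target and the break rule in Table 2, and state the expression actually used. No formula or heart rate rule is proposed here.

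In the report of the training data:
- give beta-blocker use by arm at baseline;
- report target-HR attainment separately for users and non-users within each arm;
- list sessions with a reserve at or below zero separately, outside the attainment figure.

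The cost is one check of a printed expression and one split table. Age, resting rate and beta-blocker status were already needed to set the zones. With arms of 19 and 20 the split cells will be small, so they should be read descriptively, and the pooled attainment figure becomes less clean. Training and follow-up are over, so only the reporting can change.

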### Recording Training Intensity Rating of Perceived Exertion for Each Training Session

We used the Borg Scale (ie, 6 to 20) [45,46] to solicit RPE values from participants every 2 min during training. We were interested not only in participants’ general perceived training difficulty but also in which of the 9 skills would elicit the highest RPE values from participants in the HF+C group.

**Table 1 table1:** Description of the 9 essential locomotor challenges used in training the challenge and hands-free (challenge with hands-free walking) group.

Challenge task	KineAssist interface mode	Rationale	Training practice	Task difficulty
Long stepping	KA^a^ self-drive mode	To step over common environmental hazards, for example, puddles	Using infrared laser beams, we defined a visual line on the treadmill surface in front of the participant’s feet participants instructed to take long steps, such that the heels of both feet crossed the line	If the participant was able to consistently step over the line, the distance was increased by 1-inch increments
Speeding up and slowing down	KA joystick mode	To improve the ability to speed and slow down during ambulation	The training staff the controlled the belt speed for 20 s at individual’s CWS^b^, 20 s at double their CWS, and 20 s at CWS per each minute of training	If the participant was able to successfully keep up with the fast speed, the top speed increased by 0.2 m/s
Head turns	KA self-drive mode	To simulate the need to look in different directions while walking in the community	Participants walked at their CWS. Every 10 s, staff provided instructions to turn the head either right, left, up, or down, and maintain it for 10 s	If the participant maintained walking speed with head turns, they were instructed to shake their head side-to-side or up/down for 10 s each
Variable walking speeds	KA joystick mode	To improve reactionary balance and gait speed control	KA software controlled the treadmill belt speed within a range of the participants’ CWS±0.2 m/s. Participants adapted to abrupt changes in speed	If the participant was able to successfully maintain balance and walk comfortably, speed ranges were increased by 0.2 m/s
Hurdles	KA self-drive mode	To improve ability to step over objects in the environment (eg, curb)	Participants were instructed to walk at their CWS while stepping over a hurdle positioned at height to challenge foot clearance; 5 min practice per foot	If participants consistently cleared the current hurdle height, height increased by 1-inch increments
Perturations	KA self-drive mode	To improve reactionary balance control	Participants were instructed to walk at their CWS, while experiencing abrupt disturbances (ie, brief backward accelerations) to forward progression delivered by the KA software	If participants walked through forward perturbations without experiencing disturbances (ie, missteps or backward steps), the intensity of the perturbation would be increased
Backward walking	KA self-drive mode	To improve balance control, simulate instances where stepping backward to maneuver over obstacles	Participants walked backward	If the participant successfully walked backward, they were encouraged to step faster
Walking with foam shoes	KA self-drive mode	To improve ability proprioception, to walk on uneven surfaces, and stepping height	Participants walked with foam shoes strapped to their typical footwear. Shoes ranged from 2 to 6 inches in thickness	If the participant successfully maintained their CWS, the height of the foam shoes increased from 4 to 6 inches in thickness
Narrow stepping	KA self-drive mode	To decrease reliance on external support and improve dynamic balance	Participants walked on a straight infrared while taking narrow steps at their self-selected CWS without hand support or manual assistance	If the participant successfully maintained their CWS, they were verbally encouraged to walk faster

^a^KA: KineAssist.

^b^CWS: comfortable walking speed (m/s).

**Table 2 table2:** Summary of the hands-free and challenge with hands-free walking intervention training parameters.

Intervention	Hands-free walking	Challenge+hands-free walking
Duration	6 weeks	6 weeks
Total sessions	18 sessions	18 sessions
Weekly training	3 days a week	3 days a week
Session duration	1 hour	1 hour
Intervention duration	30 min	30 min
Training speed	Comfortable walk speed at chosen BWS^a^ level	Comfortable walk speed at chosen BWS level
Intervention goal	Perform 30 min of walking at fastest 10MWT^b^ with/without BWS as prescribed	Perform 30 min of walking at fastest 10MWT with/without BWS while performing additional walking skills
Session design	5-min bouts × sets, or as long as continuously tolerated	5-min bouts × 6 sets, or 10-min bouts × 3 sets to allow for skill changes
Session goal	Target 60% to 80% of heart rate reserve during all trials	Target 60% to 80% of heart rate reserve during all trials
Locomotor challenge	Hands-free and without manual assistance	3 new randomized locomotor total challenges per day × 3 sessions=9 per week
Instruction	Maintain heart rate in the target zone while walking	Maintain heart rate in the target zone while performing different walking skills
Physiological measures monitored	Heart rate—using heart rate, monitor each minute; rate of perceived exertion—using Borg scale every 2 min; blood pressure—pre/post	Heart rate—using heart rate monitor each minute; rate of perceived exertion—using Borg scale every 2 min; blood pressure—pre/post
Additional session measurements	Total number of steps (using step watch) and distance covered (using distance wheel)	Total number of steps (using step watch) and distance covered (using distance wheel)
Rest breaks	Every 5 min if necessary; standing breaks if heart rate exceeded zone; voluntary breaks if requested by participant (rare)	Every 5 min if necessary; standing breaks if heart rate exceeded zone; voluntary breaks if requested by participant (rare)
Training personnel	Physical therapist × 1; research assistant × 1	Physical therapist × 1; research assistant × 1
Training setting	Clinical laboratory	Clinical laboratory

^a^BWS: body weight support.

^b^10MWT: 10-meter walk test.

